### 2.4. Screening/Baseline Visit (Week 0)

Potentially eligible volunteers attended the 3-h screening/baseline visit after having refrained for at least an hour from medication, food or beverages other than water. Height, weight and waist circumference were measured followed by seated blood pressure (BP) readings to determine BP eligibility. Dementia status was then assessed using the Australian version of the Mini-Modified Mental State (3MS) examination. The 3MS is a widely used tool for screening suspected dementia; a score of less than 78 was considered impaired and necessitated exclusion from the study [31].

Those who met the eligibility criteria were fitted with a Transcranial Doppler (TCD) ultrasound headpiece to assess basal cerebral haemodynamics and CVR to both hypercapnic and cognitive stimuli bilaterally in the middle cerebral artery (MCA). Participant’s performances were also recorded during cognitive testing. At the conclusion of cognitive testing, participants underwent a hypercapnic assessment of CVR in the posterior cerebral artery (PCA). A physical function assessment was then carried out before a series of six paper-based questionnaires to assess mood and general wellbeing were completed to conclude the visit. Figure 1 depicts the flowchart of the participants who were enrolled in the study. It also highlights our study population size (*n* = 80, 40 per treatment group) indicating that our treatment target has been reached.

### 2.5. Intervention and Follow-up (Week 0–14)

Participants were instructed to take two capsules of resveratrol daily, preferably at the same time with meals, and to record each intake in the assigned supplement diary in order to assist with treatment compliance. If a dose was missed, participants were able to catch up the same day but discouraged from carrying over the dose to the next day. Participants were also encouraged to maintain their habitual diet throughout the intervention; however any changes in dietary supplement and/or medication intake during the intervention were to be recorded in the supplement diary. Participants were also notified to contact the study investigators by phone if they experienced any out of the ordinary side effects, became ill during the trial period or deviated from their habitual medication use. Every four weeks participants were required to complete the Pittsburgh Sleep Quality and the Menopausal Rating Scale in their supplement diaries.

A follow-up phone call will be made at week 6–8 in order to enquire about the participant’s welfare, reports of any side-effects and changes in diet, physical activity or medication use. This call will also serve to encourage compliance, with investigators checking how participants are coping with their allocated supplement and whether or not they are consuming them as instructed, and whether their questionnaires are being filled. At the end of the trial, all remaining capsules will be counted and tallied with the corresponding diary records to confirm compliance.

### 2.6. End of Intervention Visit (Week 14)

Participants will return at the end of the 14 week intervention phase for outcome assessments of clinic BP, basal cerebral haemodynamics, CVR to hypercapnia and cognitive stimuli, cognitive performance, physical function, mood and general wellbeing. These measurements will be performed in the same order as the week 0 visit; BP will be measured before the CVR to both hypercapnic and cognitive stimuli, the physical function test and mood and general well-being using the questionnaires. They will have fasted for at least one-hour and will have been instructed to refrain from consuming their supplement on the day of their visit so as to measure sustained effects of resveratrol rather than acute, as resveratrol is removed from circulation with 12 h [32].

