## 2. Materials and Methods

### 2.1. Study Design

A randomised, double-blind, placebo-controlled (parallel comparison) dietary intervention trial of 14 weeks duration was designed to evaluate the effects of resveratrol supplementation (75 mg twice daily) on cognitive abilities, CVR and overall well-being. The dose was based on data from an acute dose response trial in those with type 2 diabetes mellitus (manuscript in preparation), in which 75 mg resveratrol elicited maximal CVR to hypercapnia when compared with 150 mg and 300 mg doses. Assessments will be made at baseline (week 0) and at the end of the 14-week intervention phase (week 14). The trial will be conducted at the Clinical Nutrition Research Centre, University of Newcastle, in New South Wales, Australia in accordance with the Declaration of Helsinki and Principles of Good Clinical Practice as outlined by the International Conference on Harmonisation. The protocol has been approved by the University of Newcastle’s Human Research Ethics Committee (H-2015-0002; approved on 13 March 2015) and registered with the Australia and New Zealand Clinical Trials Registry on 27 March 2015 (ACTRN12615000291583).

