### 2.14. Statistical Analysis

The primary outcome is the effect of resveratrol supplementation *versus* placebo on cognitive performance, determined using a composite score of all memory tests. Treatment by time effects will be determined by analysis of variance (ANOVA), or analysis of covariance (ANCOVA) in the event of interacting variables. the process of subject allocation by minimisation will have balanced age and years since cessation of menses between groups; however other baseline characteristics such as clinic BP, basal PI, BMI, 3MS score and years of education will be considered covariates if they were significantly correlated with the primary outcome.

Treatment changes in CVR to hypercapnia and/or cognitive stimuli, improvements in physical function, mood states and quality of life will be assessed using linear regressions with false rate discovery adjustments used to minimise type 1 error. In addition, to explore the potential benefits of early intervention, the magnitude of improvement following resveratrol supplementation will be compared in early (<10 years) and late (>10 years) postmenopausal women. Statistical significance for the primary outcome is set at *p* < 0.05 and false discovery rate will be applied to secondary outcomes. Statistical analyses will be performed using SPSS version 21.0 (SPSS by IBM Inc., Chicago, IL, USA).

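### Minor: holding capsules on the day of the week-14 visit does not guarantee the 12 h clearance given as the reason when a late-evening capsule precedes a morning visit

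*Protocol article*

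**What the plan says.** Section 2.6 (End of Intervention Visit) gives the rule, its purpose and its reason in one sentence. Participants will be "instructed to refrain from consuming their supplement on the day of their visit so as to measure sustained effects of resveratrol rather than acute". The reason offered for this hold is clearance time: "as resveratrol is removed from circulation with 12 h" (I read the last phrase as within 12 h). The same sentence sets the food fast in hours: "They will have fasted for at least one-hour".

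Section 2.5 governs capsule timing up to that visit. Two capsules are taken daily, "preferably at the same time with meals". On missed capsules it says: "If a dose was missed, participants were able to catch up the same day". Carrying a dose over to the next day is discouraged. The section gives no latest time for the evening capsule or for a catch-up.

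Section 2.1 takes the dose from "an acute dose response trial in those with type 2 diabetes mellitus". Its reported result was that "75 mg resveratrol elicited maximal CVR to hypercapnia when compared with 150 mg and 300 mg doses". Section 2.14 makes cognitive performance the primary outcome, "determined using a composite score of all memory tests".

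**The concern.** A calendar-day hold guarantees only the hours between midnight and the start of the visit. The stated reason needs 12 h. A woman who takes or catches up a capsule late in the evening and attends the next morning can obey every stated instruction and still arrive inside the clearance window.

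What is at stake is narrow. Residual exposure to resveratrol could arise only in the active arm, so any acute effect it had would not cancel between arms and would be read as part of the sustained effect. The outcome most exposed is CVR to hypercapnia, because that is where the article reports an acute effect, at 75 mg, the content of one capsule here. CVR is a secondary outcome. The article shows no acute effect on the primary cognitive composite.

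**Working it through.** **Inputs from the article**
- Clearance interval: 12 h (section 2.6). It rests on a cited source and cannot be recomputed from the article.
- Hold: no capsule on the calendar day of the visit (section 2.6).
- Dosing: two 75 mg capsules a day for 14 weeks, with meals preferred and same-day catch-up allowed (sections 2.1 and 2.5).
- Blood pressure: 10 min rest, then four readings 2 min apart (section 2.7), taken before the Doppler work (section 2.6).
- Doppler: 30 s basal recording before hypercapnia and before each cognitive test (section 2.8); hypercapnia for 180 s, repeated once after a 2 min interval (section 2.9).

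**Assumptions:** visit start times and capsule times, neither of which the article gives.

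**Step 1: gap from capsule to arrival.** Gap = (24:00 − time of last capsule) + visit start time. For an 08:00 start:

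| Last capsule | Gap | 12 h met? |
|---|---|---|
| 18:00 | 14 h | yes |
| 20:00 | 12 h | yes |
| 21:00 | 11 h | no |
| 22:00 | 10 h | no |
| 23:00 | 9 h | no |
| 23:59 | 8 h 1 min | no |

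**Step 2: latest capsule that still gives 12 h.** Latest time = start − 12 h.

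| Visit start | Latest capsule |
|---|---|
| 08:00 | 20:00 |
| 09:00 | 21:00 |
| 10:00 | 22:00 |
| 11:00 | 23:00 |
| 12:00 | 24:00 |

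From noon on, no capsule time allowed by the rule can fall short. Before noon, not every late capsule fails: 22:00 followed by a 10:00 start gives exactly 12 h.

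**Step 3: does the order of the visit make up the difference?** These are minimum times, with nothing added for height and weight, headpiece fitting or locating the arteries.
- Earliest Doppler: 10 + 3 × 2 = 16 min after arrival.
- Earliest cognitive test, if hypercapnia in the middle cerebral artery comes first as the wording suggests: 16 + 0.5 + 3 + 2 + 3 + 0.5 = 25 min after arrival.

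For an 08:00 arrival:
- 22:00 capsule: at least 10 h 16 min to Doppler and 10 h 25 min to the first cognitive test.
- 23:59 capsule: at least 8 h 17 min and 8 h 26 min.

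These minimum procedure times add minutes, while the shortfall at arrival can reach 12 h − 8 h 1 min = 3 h 59 min. True gaps will be somewhat longer than these minima.

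**Step 4: exposure lost if one catch-up is skipped.** 14 weeks × 7 days × 2 capsules = 196 capsules, and 1/196 = 0.5%.

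**The case against.** The strongest reply is that nothing here shows a problem in practice. A shortfall needs a morning visit and a capsule less than 12 h before it, usually away from the preferred mealtime, on one evening out of 98 days. A capsule with an evening meal between 18:00 and 20:00 leaves 12 to 14 h before even an 08:00 visit. Clinic hours and the exact participant instruction may be in the full protocol, which a journal article condenses. The 12 h is an upper bound on clearance, and the article does not show that any acute effect persists at 8 to 12 h. Its acute evidence is for CVR in people with type 2 diabetes. A rule of no capsule on the visit day is also easy to follow. The comparison with the food fast is weak, since a one-hour fast can hardly be set in any other unit.

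Most of this stands, and it is why the point is minor. It does not remove the mismatch, because the point is not that a detail is missing: the article states a rule and a reason, and the rule does not deliver the reason. The supplement diary does not settle it either. Section 2.5 has each intake recorded for compliance but does not say that clock times are entered.

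**Conclusion.** The point holds as a minor, optional improvement. Under the stated rules, 12 h off the supplement is secured only for visits starting at noon or later. For an assumed 08:00 start the guaranteed gap is about 8 h, and a 22:00 capsule leaves 10 h. How many women this affects is unknown and may be none.

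The randomised comparison, alpha and power are not affected. What is not fully secured is the description of the week-14 effects as sustained rather than acute, and that matters mainly for CVR. The conclusion rests on assumed visit and capsule times, on taking the article's 12 h at face value, and on section 2.6 being the whole instruction given to participants.

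**What to change.** Reword the instruction along these lines: take no capsule on the day of the visit, take the last capsule at least 12 h before the visit starts, and do not catch up a missed capsule after that time. Ask for the time of the last capsule at the visit and record it. No sensitivity analysis is needed; at most, report the distribution of intervals by arm.

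The cost is one reworded instruction and one recorded time. The small downside is some limit on evening dosing or on early appointments, and possibly one skipped capsule in about 196 (0.5%). The article describes the week-14 visits in the future tense, so as written the change can still be applied.

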### 2.7. Outcome Assessments

#### Clinic Blood Pressure

Participants were rested for 10 min in a seated position. Four consecutive readings of BP were taken at 2 min intervals; the first was discarded and the remaining averaged to obtain resting BP (systolic, diastolic and mean arterial pressure) and heart rate for analysis. Measurements were taken by automated oscillometry using an appropriately sized BP cuff placed over the brachial artery of the non-dominant hand (HDI Cardiovascular Profiler CR2000, Minnesota, MN, USA). BP measurements were performed by a single investigator ([name]), in accordance with international guidelines [33].

### 2.8. Transcranial Doppler Ultrasound Assessements

#### Basal Cerebral Haemodynamics

TCD is a non-invasive technique that utilises ultrasound to assess blood flow velocity in the brain. Using a TCD headpiece (Doppler-Box X, Singen, Germany), the MCA on both the left and right sides were isolated using the transtemporal window as this provides the least interference during insonation. The depth of insonation for MCA and PCA were between 45–60 mm and 60–70 mm respectively [34]. A 30-s of continuous recording of basal blood flow velocity in the MCA and PCA (maximum, minimum and mean) were obtained before hypercapnic provocation and before the start of each cognitive test. All basal blood flow velocities will be collated in spreadsheets and an average of the last 10 s of mean blood flow velocity (*x*) will be reported for use in CVR calculations. The pulsatility index (PI) of the MCA and PCA, reflecting stiffness in the cerebral vessels, is determined from the maximal velocity minus the minimum velocity and divided by the mean velocity obtained during basal conditions.

### 2.9. Cerebrovascular Responsiveness

Increases in blood flow velocity in the MCA and PCA reflect the extent of endothelial dilation in downstream anterior and posterior vessels respectively and thus is a good measure of CVR [35]. To assess CVR, participants inhaled a carbogen gas mixture (5% CO_2_, 95% O_2_) through a two-way non-rebreathing mouthpiece for 180 s, resulting in an acute increase in blood flow velocity. The TCD recorded bilateral beat-to-beat mean blood flow velocities during the hypercapnic provocation. Our group has shown great reproducibility and thus the procedure was only repeated once for reliability with a 2 min interval for washout.

The TCD headpiece was kept in position throughout the cognitive test battery to assess CVR to cognitive stimuli in the MCA and was recorded during each cognitive task

Data will be stored on the computer hard drive until subsequent analysis. Each task, including hypercapnia, recordings would be smoothed and analysed in TableCurve™ using data spline estimation with Loess at 20% for hypercapnic assessment and 10%, for cognitive tasks, (TableCurve 2D by Systat Software Inc., San Jose, CA, USA) to determine the peak increase in mean flow velocity (y). CVR is calculated as a percentage using the equation$\;\frac{y-x}{x}\times 100$.

### 2.10. Cognitive Performance

The neuropsychological test battery consisted of four tests, The Rey Auditory Verbal Learning Test (RAVLT) [36], the Cambridge Semantic Memory Battery [37], the Double Span [38] and the Trail Making Task (TMT) [39]. The composition of the test battery was chosen such that it would assess those cognitive domains known to be negatively affected by reductions of circulating estrogen in women, namely semantic [40], verbal [41] and visual spatial working memory [42,43] as well as executive function, shown to decline with age irrespective of gender [44]. Importantly these tests also reflect the ability to perform everyday tasks with a decline indicating a loss of independence in these women. Table 2 outlines these tests, describing the cognitive domains targeted, the procedure and scoring profiles.

### 2.11. Assessment of Mood

Participant’s mood states were assessed using two different indexes, the Profile of Mood States (POMS-V2) and the Center for Epidemiological Studies Depression Scale (CES-D). The POMS questionnaire assessed how the participant was feeling over the last week including the day of the visit through 65-adjectives that the participant rated on a 5-point Likert scale (1 being “not at all” and 5 being “extremely”). The POMS Standard has proven to be an excellent measure of mood states and their fluctuations [45]. The CES-D scale is a commonly used tool to characterize depressive symptoms in the general population [46] and the sensitivity ideal for detecting depression in postmenopausal women [47]. The 20-item scale measures major depressive symptomatology of participants, including depressive mood, feelings of guilt and worthlessness, psychomotor retardation, loss of appetite and sleep disturbances.

### 2.12. Physical Function Assessment

The physical function test battery is a validated measure of functional performance of daily living activities in community living older adults consisting of nine tasks [48]. For each task, the time taken to complete was recorded. Participants were required to write a legible sentence, mimic eating by picking up kidney beans with a teaspoon from a bowl and placing them in another while they remain stationary, lifting a heavy book from waist level and placing on a cabinet at shoulder level while remaining seated, put on and remove a coat (A standard lab coat was used to maintain consistency), pick up a 50 cent coin from the floor, pivot 360°, walk 15 metres and climb flights of stairs. Assistive devices are permitted in the locomotive tasks. Higher scores equated to better performances.

### 2.13. Assessment of Overall Well-Being

Overall wellbeing was assessed through a series of four different questionnaires, designed to assess varying aspects of a participant’s general living. Participant’s pain symptomatology was assessed through the Short-form McGill Pain questionnaire [49]. Sleep quality was assessed through the Pittsburgh Sleep Quality Index [50], Menopausal symptoms were assessed using the Menopausal Rating Scale (MRS) as this has been shown to be effective in measuring treatment effects on quality of life across the full range of severity of complaints in ageing women [51] and the participants own perception of their physical and mental health were also recorded using the Short-form 36 (SF-36) Health Survey, a validated questionnaire in menopausal women [52].

### 2.14. Statistical Analysis

The primary outcome is the effect of resveratrol supplementation *versus* placebo on cognitive performance, determined using a composite score of all memory tests. Treatment by time effects will be determined by analysis of variance (ANOVA), or analysis of covariance (ANCOVA) in the event of interacting variables. the process of subject allocation by minimisation will have balanced age and years since cessation of menses between groups; however other baseline characteristics such as clinic BP, basal PI, BMI, 3MS score and years of education will be considered covariates if they were significantly correlated with the primary outcome.

Treatment changes in CVR to hypercapnia and/or cognitive stimuli, improvements in physical function, mood states and quality of life will be assessed using linear regressions with false rate discovery adjustments used to minimise type 1 error. In addition, to explore the potential benefits of early intervention, the magnitude of improvement following resveratrol supplementation will be compared in early (<10 years) and late (>10 years) postmenopausal women. Statistical significance for the primary outcome is set at *p* < 0.05 and false discovery rate will be applied to secondary outcomes. Statistical analyses will be performed using SPSS version 21.0 (SPSS by IBM Inc., Chicago, IL, USA).

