### 2.2. Study Population

Healthy postmenopausal women from the general public residing in the Hunter region of New South Wales were invited to participate following expressions of interest to approved newspaper and radio campaigns. Each volunteer was first provided with an information statement outlining the study objectives and procedures. A health and lifestyle questionnaire that collected information pertaining to their menopausal status, medication and dietary supplement use and current perception of their cognitive status was completed by interested parties. Upon returning the questionnaire, a study investigator pre-screened volunteers via telephone to determine their potential suitability, as described in Table 1, and to invite them in for a screening/baseline visit at the research centre. They were also encouraged to consult with their medical practitioner regarding their intention to participate in this intervention prior to their first visit. Written informed consent was obtained at start of the screening/baseline visit.

Our power calculations (G*Power) [29] showed that 74 participants would give 80% chance of detecting a statistically significant difference (*p* < 0.05) of medium effect size (standardized difference = 0.67) in cognitive performance (composite score) between Resveratrol and placebo treatments. To allow for attrition, we aimed to recruit 80 women.

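### The primary test compares change from baseline and commits to no adjustment for the baseline composite, so it gives up precision that the data already collected would provide

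*Protocol article*

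**What the plan says.** All references are to the protocol article.

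- **Primary model (section 2.14, Statistical Analysis):** "Treatment by time effects will be determined by analysis of variance (ANOVA), or analysis of covariance (ANCOVA) in the event of interacting variables". The outcome is a composite of the memory tests, and "Statistical significance for the primary outcome is set at *p* < 0.05".
- **Covariates (section 2.14):** "other baseline characteristics such as clinic BP, basal PI, BMI, 3MS score and years of education will be considered covariates", on condition that each correlates significantly with the primary outcome. Age and years since menses are described as already balanced by minimisation and are not on this list. The baseline composite is not named.
- **Visits (section 2.1, Study Design):** "Assessments will be made at baseline (week 0) and at the end of the 14-week intervention phase (week 14").
- **Sample size (section 2.2, Study Population):** "74 participants would give 80% chance of detecting a statistically significant difference" of "medium effect size (standardized difference = 0.67) in cognitive performance (composite score"). The section does not say whether the SD behind 0.67 is that of the score or of its change.

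**The concern.** With one baseline and one follow-up value per woman, the treatment-by-time F-test in a repeated-measures ANOVA is algebraically the two-sample t-test on change from baseline. That test subtracts the whole baseline value, which is the same as fixing the baseline slope at 1. ANCOVA estimates the slope. Where the true slope is below 1, subtraction over-corrects and leaves avoidable noise in the treatment comparison.

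Minimisation used only age and years since menses (section 2.3), and women aged 45 to 85 were eligible (Table 1). Baseline cognition can therefore vary widely and differ between arms by chance. The covariate that addresses this most directly is the week-0 value of the outcome itself, and the text does not commit to it.

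The model behind the primary p-value is also left open. Whether ANOVA or ANCOVA is used, and with which covariates, depends on an undefined condition and on significance screening in the trial's own data. At stake is the precision of the primary comparison and a clear statement of which model produces it.

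**Working it through.** **Inputs.** Primary alpha 0.05 (section 2.14), taken as two-sided because sidedness is not stated. 74 evaluable women for 80% power at a standardized difference of 0.67 (section 2.2). Equal arms: "study population size (*n* = 80, 40 per treatment group") (section 2.4), so 74 evaluable is 37 per arm. Two visits (section 2.1). *Assumed:* the correlation rho between the week-0 and week-14 composite, which the document does not give and which is shown as a range; and equal variances at the two visits, relaxed in step 5.

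**1. Reproduce the plan's figure.** Two-sample t-test, noncentral t, noncentrality = d × √(n/2) with n per arm. With d = 0.67 and n = 37 this is 0.67 × √18.5 = 2.88 on 72 df, giving power 81.1%. The smallest size reaching 80% is 36 per arm, or 72 in total. The stated 74 is within two women of this, so it reproduces as an unadjusted two-sample comparison.

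**2. Variance of each analysis.** Let the SD of the score be 1 at both visits.
- Change score: 1 + 1 − 2rho = 2(1 − rho).
- ANCOVA on the baseline composite: 1 − rho².
- Ratio: (1 − rho²) / [2(1 − rho)] = (1 + rho)/2.

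This gives 0.75, 0.85, 0.90 and 0.95 at rho 0.5, 0.7, 0.8 and 0.9, so the variance falls by 25%, 15%, 10% and 5%.

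**3. Power if 0.67 is in SDs of change.** The effective d under ANCOVA is 0.67 / √((1 + rho)/2), with one further df spent on the covariate (71 df), 37 per arm.

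| rho | effective d | change-score test | ANCOVA | total N for 80% with ANCOVA (change score: 72) |
|---|---|---|---|---|
| 0.5 | 0.774 | 81.1% | 90.7% | 56 |
| 0.7 | 0.727 | 81.1% | 86.9% | 62 |
| 0.8 | 0.706 | 81.1% | 85.0% | 66 |
| 0.9 | 0.687 | 81.1% | 83.1% | 70 |

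**4. Power if 0.67 is in SDs of the score.** The effective d is 0.67 / √(2(1 − rho)) for change and 0.67 / √(1 − rho²) for ANCOVA, 37 per arm.

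| rho | change-score test | ANCOVA |
|---|---|---|
| 0.3 | 67.1% | 84.6% |
| 0.4 | 73.7% | 87.3% |
| 0.5 | 81.1% | 90.7% |
| 0.7 | 95.6% | 97.8% |
| 0.8 | 99.4% | 99.7% |

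The two readings coincide at rho 0.5, where the SD of change equals the SD of the score. A simulation of 20,000 trials gave 81.3% against 90.4% at rho 0.5, and 95.6% against 97.6% at rho 0.7 on the score scale, in line with the formulas.

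**5. Unequal variances.** Let k be the week-14 SD divided by the week-0 SD, with the week-0 SD equal to 1. The change variance is 1 + k² − 2·rho·k, the ANCOVA variance is k²(1 − rho²), and the difference is (1 − rho·k)², which is never negative. At rho 0.8:
- k = 1.1: 0.450 against 0.436, a saving of 3%.
- k = 1.0: 0.400 against 0.360, a saving of 10%.
- k = 0.9: 0.370 against 0.292, a saving of 21%.

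The direction holds whatever k is, apart from the one df; the size does not.

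**The case against.** The strongest reply is that nothing here is invalid. In a randomised two-visit trial the test of change is unbiased and keeps its type I error, and with 0.67 in SDs of change it meets the stated 80% at 74 women. The covariate list is open-ended, 3MS is a partial proxy for baseline cognition, and a condensed article may leave the exact covariate set to a fuller document. The gain also rests on quantities the document does not give, and it shrinks to 2 points at rho 0.9 on the change scale, or 0.3 points at rho 0.8 on the score scale. All of this stands, and it limits the point to lost efficiency of uncertain size. It does not remove the point: the article does state the primary model, and that model is by default a change-score test with ANCOVA only conditional.

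Three stronger readings are tempting and are not supported.

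- *That the rule for using ANCOVA is reversed,* because a covariate that interacts with treatment breaks the common-slope assumption. The next sentence of section 2.14 admits covariates by their correlation with the primary outcome, which is a prognostic criterion. The word interacting is more likely loose than a reversed rule. What remains is that the condition is undefined and the screening uses trial data.
- *That the secondary analyses also ignore baseline.* Section 2.14 says only that linear regressions will be used and gives no model terms. Sleep quality and menopausal symptoms are also recorded every four weeks (section 2.5), so the two-visit algebra does not carry over to them automatically.
- *That the trial is underpowered.* The planned test falls below 80% if 0.67 is in SDs of the score and rho is below 0.5. Neither condition is documented.

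**Conclusion.** The point holds as a recommendation about efficiency and about fixing the model in advance. As written, the default primary analysis is a test of change that does not commit to the baseline composite, and the route to ANCOVA depends on the data. Baseline-adjusted ANCOVA is at least as precise for any correlation and any variance ratio, apart from one degree of freedom.

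Confidence is high in the direction and modest in the size. With equal variances, 37 per arm and 0.67 in SDs of change, the gain runs from about 10 percentage points at rho 0.5 to 2 at rho 0.9. With 0.67 in SDs of the score, it runs from about 17 points at rho 0.3 to almost nothing at rho 0.8.

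**What to change.** Before unblinding, state a single primary analysis in section 2.14: ANCOVA of the week-14 composite on treatment, with the baseline composite and the two minimisation factors (age and years since menses) as covariates, fitted unconditionally. Delete the clause that makes ANCOVA depend on interacting variables, and do not let significance screening of other covariates decide the primary model. A model with further covariates can be kept as a labelled sensitivity analysis. It would also help to say in section 2.2 whether 0.67 is in SDs of the score or of the change.

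The cost is a few sentences. The composite is already measured at week 0, no extra participants or visits are needed, and section 2.3 keeps the blind until analysis is complete, so the change can still be made without knowledge of the results by arm.
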